**Fig. 2 Fig2:**
[figure not shown]
SPIRIT figure of trial interventions and timings

### Sample size

In a cohort of 368 preterm infants born between 24 to 30 weeks of gestation, the standard deviation for the duration of mechanical ventilation was 3.83 days [27]. The median duration of ventilation in our NICU was 12 days (mean 19 days). Randomisation of 70 infants allows us to detect a decrease in the duration of mechanical ventilation of three days with a 90% power at the 5% significance level.

At the request of the ethics committee, an interim analysis will be carried out after half the sample has been recruited to review if enough data have been gained at that point. The analysis will be performed by an independent researcher not involved in the project to avoid introducing bias to our data. The research team will be blinded to the results of the interim analysis unless there are any significant findings.

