Over the past decade, increased knowledge of the risks related to mechanical ventilation and advances in non-invasive respiratory support have resulted in the reduction in the duration of mechanical ventilation [31]. Nevertheless, historical data from our unit for the period 2015–2020 demonstrated that the median duration of mechanical ventilation for preterm infants born less than 31 weeks gestation was 12 days. Hence, our study is powered to detect a decrease in the duration of mechanical ventilation of 3 days between the two treatment groups.

In conclusion, if this study demonstrates that CLAC is associated with earlier extubation and a shorter duration of mechanical ventilation, that could have significant impact on long-term respiratory outcomes of preterm infants.

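### The 90% power for a 3-day reduction uses an SD of 3.83 days that does not fit the recruiting unit's own mean of 19 and median of 12 days

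*Protocol article*

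**What the plan says.** Methods, Sample size, gives three statements in a row.

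- The planning SD comes from outside the unit: "the standard deviation for the duration of mechanical ventilation was 3.83 days". Its source is an external cohort of 368 infants of 24–30 weeks' gestation.
- The unit's own experience follows: "The median duration of ventilation in our NICU was 12 days (mean 19 days".
- The power claim, made for a 5% significance level, closes the paragraph: "Randomisation of 70 infants allows us to detect a decrease in the duration of mechanical ventilation of three days with a 90% power".

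The Discussion says that the 12-day median comes from the unit's 2015–2020 records: "the median duration of mechanical ventilation for preterm infants born less than 31 weeks gestation was 12 days". It then restates the claim: "Hence, our study is powered to detect a decrease in the duration of mechanical ventilation of 3 days between the two treatment groups".

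Three other sections matter. Setting names one neonatal unit as the only site. Statistical analysis assigns the t test to normally distributed data and the Mann-Whitney test to skewed data. Primary outcome measure counts time from enrolment to successful extubation or, for infants still ventilated after day 28, to the first extubation attempt.

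**The concern.** A mean 7 days above the median describes a long right tail. An SD of 3.83 days describes a narrow distribution. One population cannot have both, and every trial infant comes from the unit with the long tail. A normal distribution with mean 19 and SD 3.83 would put about 3% of infants below 12 days [(12 − 19)/3.83 = −1.83], whereas the reported median puts half of them there.

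The sample size rests wholly on this SD, for the primary outcome. If the true spread is about twice the planning value or more, the trial would more often miss a real 3-day benefit than find it. The published 90% would then give a non-significant result more weight than it can bear.

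**Working it through.** **Inputs.** SD 3.83 days, difference 3 days, power 90%, significance 5%, total 70, unit median 12 and mean 19 (all from Sample size); 1:1 allocation (Methods). The article does not state sidedness.

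**Step 1: reproduce 70.** For two means, n per arm = 2 × (z₀.₉₇₅ + z₀.₉₀)² × (SD/difference)² = 2 × (1.960 + 1.282)² × (3.83/3)² = 34.3, so 35 per arm and 70 in total. A one-sided test would need 28 per arm (56 in total), so the calculation was two-sided. Exact t-test power with 35 per arm is 89.8%. The plan's figure reproduces.

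**Step 2: the SD implied by the unit's figures.** For any distribution, |mean − median| ≤ E|X − median| ≤ E|X − mean| ≤ SD. The second step holds because the median minimises expected absolute deviation. Hence SD ≥ 19 − 12 = 7 days. If both values were rounded to whole days, the gap could be as small as 18.5 − 12.5 = 6 days, so SD ≥ 6.

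**Step 3: SDs under assumed shapes.** The article gives no SD for the unit, so these are assumptions.

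- Lognormal with median 12 and mean 19: σ² = 2 ln(19/12) = 0.919, σ = 0.96, SD = 19 × √(e^0.919 − 1) = 23.3 days.
- Gamma with the same mean and median: shape 0.81, SD = 19/√0.81 ≈ 21.1 days.

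**Step 4: t-test power for 3 days.** Noncentral t, 68 degrees of freedom, noncentrality 3/(SD × √(2/35)), two-sided 5%. The last column is the difference detectable with 90% power.

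| SD (days) | Basis | Power | Detectable difference |
|---|---|---|---|
| 3.83 | external cohort | 90% | 3.0 days |
| 6 | floor if both figures are rounded | 54% | 4.7 days |
| 7 | floor from the figures as printed | 42% | 5.5 days |
| 10 | illustration | 24% | 7.9 days |
| 15 | illustration | 13% | 11.8 days |
| 21.1 | assumed gamma | 9% | 16.6 days |
| 23.3 | assumed lognormal | 8% | 18.3 days |

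**Step 5: Mann-Whitney power.** Simulated with 35 per arm, 10,000 trials per scenario. The result depends on what a 3-day effect means.

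| Effect | Lognormal | Gamma |
|---|---|---|
| Mean falls from 19 to 16, proportionally | 11% | 8% |
| Median falls from 12 to 9, proportionally | 23% | 14% |
| Every duration 3 days shorter | 25% | 19% |

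**Step 6: a deliberately favourable case.** Cap every lognormal duration at 28 days, which is harsher than the outcome definition, then apply a full 3-day shift. The SD falls to about 9 days. Power is about 28% by t test and 36% by Mann-Whitney.

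**The case against.** The best defence has four parts.

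1. **The SD is cited, and nothing shows it to be wrong for its source.** This stands. A reader might infer that the cited cohort's figure is an error, but the article does not allow that conclusion. It shows only that the figure does not carry over to this unit.

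2. **42% is not a ceiling.** A reader might infer that power is at most 42%. That does not follow. It is the t-test figure at SD 7, and rounding could raise it to 54%. Nor does an SD floor bound Mann-Whitney power: an artificial two-point distribution (12 or 26 days, SD 7) with a constant 3-day shift gives about 96%. That shape is not a realistic one for ventilation times, and the skewed shapes tried give 8–25%.

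3. **The low figures rest on assumed shapes and on historical durations.** A reader might infer that true power is about 10%. The article reports only a mean and a median, so no single value can be fixed. The trial outcome starts at enrolment, up to 48 h after ventilation begins, and for infants ventilated beyond day 28 ends at the first extubation attempt, so its spread may be smaller than the historical one. The 28-day cap in step 6 goes further than this and still leaves power far below 90%.

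4. **The mean and median may not share a source.** The Discussion gives period and gestation for the median only. The Sample size section reports both in one sentence, so a common source is a fair inference, though not a stated fact.

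**Conclusion.** The concern holds. The formula and arithmetic are sound, but the 90% power claim is not supported for the population being recruited. The unit's own figures imply an SD of at least about 7 days (6 allowing for rounding) against the 3.83 used. On the test that produced the sample size, that means about 42% (54%) power for 3 days, and less at any larger SD. With the skewed shapes tried, power is roughly 8–25% depending on the test and on how the effect is expressed; those values illustrate a range and are not estimates. The conclusion assumes that the mean and median describe the same infants and that the trial's durations resemble the unit's recent ones. Nothing elsewhere in the article repairs the claim.

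**What to change.** 1. Withdraw the 90% power statement in Sample size and its repetition in the Discussion.
2. Restate the power and the detectable difference for 70 infants from the unit's own 2015–2020 ventilation data, using the planned primary test. Simulation would do. So would a ratio of durations on the log scale: at the assumed lognormal σ of 0.96, 90% power needs a ratio of about exp(−3.242 × 0.96 × √(2/35)) ≈ 0.48.
3. Say whether the 3 days refers to the mean, the median or a constant shift, since the power depends on it.
4. State in the protocol and in the final report that a non-significant result does not exclude a 3-day benefit.

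The cost is a change of wording and a short simulation on data the unit should already hold. It needs no extra infants and no change in care. It corrects the description of the trial without raising its power, and the stated power will look less favourable.

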## Roles and responsibilities of study management committees, groups, and individuals

There are no committees or steering groups involved in the management of this study, but all the neonatal consultants have oversight of the study. The chief investigator and sponsor will monitor and audit the conduct of this research and will ensure that appropriate standards and reporting are adhered to (p6, 59–60). All the neonatal consultants have oversight of the study (p6, 70–71). In addition to this, an independent researcher not involved in the project will review trial data upon recruiting half of planned patients. The researcher will evaluate differences in the primary outcome to decide whether enough data have been gained at that point. The research team will remain blinded to the results of the interim analysis unless there are any significant findings (p12, 204–208). This is a non-blinded, randomised, superiority trial.

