### Statistical analysis

Data will be compared between infants in the intervention group (closed-loop automated oxygen control) and infants in the control group (manual oxygen control). The data will be assessed for normality; Student’s *t* test will be used for normally distributed data and Mann-Whitney *U* test for skewed data. Categorical data will be assessed using the Fisher two-tailed exact test. Analysis will be undertaken using SPSS software (SPSS Inc., Chicago, IL, USA). Data analysis will be conducted on an intention-to-treat basis, and missing data will not be imputed. Analysis will be undertaken to a researcher blind to which arm the infants was randomised.

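### The half-way comparison of the primary outcome has no stated threshold or adjusted final level; read literally, overall type I error is about 8.3%, not 5%

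*Protocol article*

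**What the plan says.** Two sections of the protocol article describe one interim analysis, requested by the ethics committee.

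- **Sample size**, on timing and purpose: "an interim analysis will be carried out after half the sample has been recruited to review if enough data have been gained at that point".
- **Roles and responsibilities of study management committees, groups, and individuals**, on what is compared and why: "The researcher will evaluate differences in the primary outcome to decide whether enough data have been gained at that point". This section also places the review at the recruitment of half the planned patients.
- **Sample size**, on what follows: "The research team will be blinded to the results of the interim analysis unless there are any significant findings".

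The only significance level in the article is in the power statement in Sample size, which claims to "detect a decrease in the duration of mechanical ventilation of three days" "with a 90% power at the 5% significance level". Statistical analysis names the tests (Student's t or Mann-Whitney for continuous data), says that missing data are not imputed, and makes no allowance for a second look. Primary outcome measure runs the outcome from enrolment to successful extubation.

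**The concern.** An arm comparison of the primary outcome, a decision on whether the data suffice and unblinding on significance together make an efficacy look with a route to early stopping, although the article never uses the word stop. The independent researcher has no level to apply other than 5%. If 5% is used at half-way and again at the end, the trial has two chances of a false positive and the stated 5% no longer describes it. A trial that ends at about 17 infants per arm because it crossed an unadjusted threshold will also, on average, report too large an effect.

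Timing adds a smaller problem. An infant still ventilated at the cut has no value for the primary outcome, and such infants tend to be those ventilated longer. Leaving them out of the look is therefore not neutral.

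**Working it through.** **Inputs from the article.** Difference 3 days, SD 3.83 days, power 90%, level 5%, total 70 (Sample size); 1:1 allocation (Methods); median ventilation in the unit 12 days, mean 19 days (Sample size).

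**Assumptions.** The primary test is two-sided. The article says so only for categorical data ("Categorical data will be assessed using the Fisher two-tailed exact test"), but a two-sided calculation gives 70 and a one-sided one gives 56. Recruitment rate is not stated; 1 to 4 infants a month is assumed.

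**1. The stated sample size.** n per arm = 2 × [SD × (1.960 + 1.282) / difference]² = 2 × [3.83 × 3.242 / 3]² = 34.25, rounded up to 35, so 70 in total. The figure reproduces as a fixed, single-look design. Power at 35 per arm is 90.6% (normal approximation) or 89.8% (t test).

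**2. Type I error with two looks at 0.05.** Under no effect, the interim and final test statistics are bivariate normal with correlation √(information fraction). At half information the correlation is √0.5 = 0.707, and the chance that either statistic exceeds 1.96 in absolute value is:

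| Information fraction at interim | Overall two-sided error |
|---|---|
| 0.5 | 8.3% |
| 0.4 | 8.6% |
| 0.3 | 8.9% |

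A simulation with the Mann-Whitney test on lognormal data (17 and 18 infants at the interim, 35 per arm at the end, 20,000 runs) also gives 8.3%, so the result does not depend on normal data.

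**3. What would cross at the interim.** With 17 and 18 infants, the smallest difference reaching p<0.05 is t(33) × SD × √(1/17 + 1/18) = 2.0345 × 3.83 × 0.3382 = 2.6 days.

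**4. Overstatement after an early stop.** With 17.5 per arm the standard error is 3.83 × √(2/17.5) = 1.295 days, and the normal threshold is 1.96 × 1.295 = 2.54 days. If the true difference is 3 days, the chance of crossing is about 64%. The mean estimate among trials that cross is 3 + 1.295 × φ(−0.357) / 0.639 = 3 + 1.295 × 0.374 / 0.639 = 3.76 days, about a quarter too large.

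**5. Infants still ventilated at the cut.** Expected number = recruits per month × 19 / 30.4. This is 0.6 at one a month and 2.5 at four a month, so roughly 1 to 3 of 35.

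**6. Boundaries that hold 5% overall.**

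| Rule | Interim p | Final p | Power at 70 |
|---|---|---|---|
| O'Brien-Fleming | <0.0052 | <0.0480 | 90.4% |
| Haybittle-Peto | <0.001 | <0.0498 | 90.6% |
| Pocock | <0.0294 | <0.0294 | 87.7% |

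The first two fit within 70 infants on the protocol's inputs. Pocock would need about 76.

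**The case against.** The strongest reply is that 8.3% is conditional. The 5% belongs to the power statement. No sentence says that the interim is tested at 5% or that the final test keeps the full 5%, and a boundary is commonly placed in an analysis plan, which is not shown. A total of 70 does not prove that adjustment is absent either, because O'Brien-Fleming or Haybittle-Peto would also fit. This stands as a limit on certainty. It does not remove the point: the article itself fixes the look, its decision and its unblinding trigger, and the only level it offers is 5%.

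On timing, the wording in Sample size could be read as defining which infants are analysed rather than when the data are cut, although the roles section ties the review to the moment of recruitment. Few infants are affected, and they include some just enrolled who may be extubated within days. They tend towards longer durations but are not long by definition.

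A reader might also infer that the interim ignores safety, and that early deaths would count as short ventilation and so favour the arm with more of them. The documents do not support either. The roles section says that trial data are reviewed, and no passage excludes deaths or serious adverse events (SAEs). The Safety section gives a separate SAE route to the sponsor. The article does not say how death before extubation enters the outcome; with no imputation, such an infant might equally have no value. It is also tempting to say that only an implausibly large difference could cross at half-way. On the protocol's own SD the threshold is about 2.6 days, below the 3-day design effect.

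**Conclusion.** The point holds for the missing threshold. Read as written, with significance at 0.05 at both looks and a positive claim allowed at either, overall two-sided type I error is about 8.3% against a stated 5%, or 8.6 to 8.9% if the interim carries only 40 to 30% of the information. The inflation does not depend on the SD; the 2.6-day threshold and the 3.76-day average estimate do, and rest on 3.83 days. An adjustment recorded elsewhere would remove the inflation, but the article shows none. This should be settled before the look takes place.

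The recruitment trigger is a real but modest weakness: roughly 1 to 3 of 35 infants under assumed recruitment rates.

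On safety, it can be said only that none is specified for the interim: the primary outcome is the sole variable named, and the article states that "There are no committees or steering groups involved in the management of this study". That calls for clarification and is not a demonstrated error.

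**What to change.** 1. State the boundary and the final level before the interim. Either O'Brien-Fleming (p<0.005 at the interim, p<0.048 at the end) or Haybittle-Peto (p<0.001, then about 0.05) would do.
2. Make crossing that boundary the condition for unblinding the research team, in place of the reference to significant findings, in both sections that describe the look.
3. Run the look once the first 35 infants have reached the primary endpoint.
4. Say whether the same independent researcher sees deaths and SAEs by arm at that look.

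The cost is a few sentences, a wait of some weeks for the last of the 35 outcomes, and a slightly stricter final level. Against the single-look power of 90.6%, O'Brien-Fleming loses about 0.2 percentage points and Haybittle-Peto almost nothing. No further infants are needed, and the independent researcher is already in the plan.

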### Data collection

Demographic and outcome data will be collected from the clinical records and recorded under a unique study identifier number. Basic epidemiologic parameters such as gestational age at birth, birth weight, corrected gestational age, postnatal age and weight at study enrolment, use of antenatal steroids, mode of delivery, doses of surfactant administered, birth plurality and associated comorbidities that may impact on the duration of mechanical ventilation, for example patent ductus arteriosus and infection, will be recorded for each infant. Oxygen saturation and FiO_2_ data will be downloaded from the ventilators. Paper data will be stored in a locked filling cabinet. Patient de-identified electronic data will be stored in password protected computers and on encrypted devices.

### Statistical analysis

Data will be compared between infants in the intervention group (closed-loop automated oxygen control) and infants in the control group (manual oxygen control). The data will be assessed for normality; Student’s *t* test will be used for normally distributed data and Mann-Whitney *U* test for skewed data. Categorical data will be assessed using the Fisher two-tailed exact test. Analysis will be undertaken using SPSS software (SPSS Inc., Chicago, IL, USA). Data analysis will be conducted on an intention-to-treat basis, and missing data will not be imputed. Analysis will be undertaken to a researcher blind to which arm the infants was randomised.

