### Randomisation

The randomisation sequence is generated by using an online randomisation generator and concealed in sealed opaque envelopes. This is done by a person independent of the research team who is not involved in the study.

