### Primary outcome measure

The primary outcome measure is the duration of mechanical ventilation. The primary outcome measure is the duration of mechanical ventilation from enrolment to the study until successful extubation. Extubation failure is defined as the need for reintubation within 48 h. For infants who fail extubation, they continue in their initial study arm if they are less than 28 days old, and the time they remain ventilated is counted towards the total duration of mechanical ventilation. For infants that remain ventilated beyond day 28 of life, the study continues till their first extubation attempt, and that period represents the primary outcome measure. Currently at KCH, the CLAC algorithm is used only for mechanically ventilated infants and in the context of clinical research studies. Hence, automatic oxygen control will be discontinued following extubation. Non-invasive ventilation modes will be delivered via the SLE6000 ventilators, and the control of the inspired oxygen concentration will be performed manually.

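### The primary test is unadjusted and chosen by a normality check, although skew is already known and gestational age is collected: a valid test, but it loses precision and does not by itself estimate the 3-day target

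*Protocol article*

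**What the plan says.** The Primary outcome measure section defines the endpoint: "The primary outcome measure is the duration of mechanical ventilation from enrolment to the study until successful extubation". The Statistical analysis section gives one rule for continuous data. First, "The data will be assessed for normality". Then Student's t "test will be used for normally distributed data and Mann-Whitney" U for skewed data. It names no covariate for either test.

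The Sample size section supplies the planning figures. In an external cohort "the standard deviation for the duration of mechanical ventilation was 3.83 days". For the trial's own unit it reports: "The median duration of ventilation in our NICU was 12 days (mean 19 days". It states that 70 infants "allows us to detect a decrease in the duration of mechanical ventilation of three days", with 90% power at the 5% level.

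The Data collection section lists "gestational age at birth, birth weight, corrected gestational age, postnatal age and weight at study enrolment" among the baseline items recorded. Nothing in the article brings any of them into the analysis. On allocation, the Randomisation section says "The randomisation sequence is generated by using an online randomisation generator" and mentions no stratification factor.

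**The concern.** Three features of the stated rule deserve attention.

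- **The check asks a question the plan has already answered.** A mean 7 days above the median is clear right skew. Testing the trial data for it again adds nothing, and it formally leaves open whether the primary comparison is of means or of ranks.
- **The test that will almost surely be chosen does not measure the target.** The planned effect is 3 days. Mann-Whitney on its own gives a p-value and no difference in days.
- **A probable strong predictor is collected and not used.** In infants born before 31 weeks, gestational age is likely to drive ventilation time. With 35 per arm and no stratification described, the arms can differ on it by chance, and an unadjusted comparison carries that difference into the result. Leaving it out also gives up precision that the trial could have without recruiting anyone.

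**Working it through.** **Inputs from the protocol article.** N = 70, allocated 1:1, so 35 per arm; target 3 days; SD 3.83; power 90%; 5% level; unit median 12 and mean 19 days.

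**Assumption.** R², the share of variance in log duration explained by gestational age, is not in the document. I use 0.2 to 0.5.

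**1. The plan's own figure.** n per arm = 2 × [3.83 × (1.960 + 1.282) / 3]² = 34.25, rounded up to 35, total 70. This reproduces, two-sided. The sample size is that of an unadjusted comparison of means.

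**2. Skew.** A lognormal with median 12 and mean 19 has log-scale SD σ = √(2 ln(19/12)) = 0.959. In simulated trials from it (35 per arm, 5,000 per setting), a Shapiro-Wilk check in each arm rejected normality in essentially every trial. The rule therefore leads to Mann-Whitney.

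**3. Validity.** In the same simulations with no treatment effect, the two-stage rule rejected in 4.6% to 5.4% of trials.

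**4. Chance imbalance.** With simple randomisation, the difference in mean gestational age, in SD units, has standard error √(4/70) = 0.239. So P(|d| > 0.3) = P(|Z| > 1.255) = 0.21.

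An imbalance d multiplies the median by exp(−d × √R² × σ):

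| R² | log shift at d = 0.3 | days off a median of 12 | d needed for 12 to 9 | probability |
|---|---|---|---|---|
| 0.2 | 0.129 | 1.4 | 0.67 | 0.5% |
| 0.4 | 0.182 | 2.0 | 0.47 | 5% |
| 0.5 | 0.203 | 2.2 | 0.42 | 8% |

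The fourth column is ln(12/9) / (σ√R²) = 0.288 / (0.959√R²). The last column counts imbalance in either direction, so it covers a spurious ratio of 0.75 or its inverse.

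**5. Conditional error.** Given an imbalance of 0.5 SD (about 4% of trials), the type I error of an unadjusted test is about 13%, 17% and 25% for R² of 0.2, 0.3 and 0.5. At 0.25 SD it stays at 4% to 5%.

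**6. Gain from a linear model of log duration.** The unadjusted SE is 0.959 × 0.239 = 0.229. Adjustment multiplies it by √(1 − R²), which is 0.89 at R² = 0.2 and 0.71 at 0.5, a cut of 11% to 29%. This is the precision of 70/(1 − R²) = 88 to 140 infants analysed unadjusted. Power for a median of 12 against 9 (noncentral t) rises from 24% to 28% and 42%. Simulation agreed: Mann-Whitney about 22%, adjusted model 28% and 41%.

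**7. Gain from proportional-odds regression.** The figures in step 6 do not carry over. In a small simulation at R² = 0.2 (150 trials), the mean SE of the log odds ratio was 0.42 unadjusted and 0.43 adjusted, while power rose from 19% to 27%. Adjustment enlarges the conditional effect; it does not narrow the interval.

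**The case against.** The strongest reply is that this is a journal article. Covariates, effect estimates and intervals are often left to the full protocol or the SAP, and the text does not forbid adjustment, stratification or a Hodges-Lehmann shift in days. That stands in part. Silence on stratification does not show that there is none, so the imbalance figures hold only if allocation is unstratified. An estimate in days could also be added to Mann-Whitney. But the article is not silent on the primary test. It states the selection rule and both candidate tests, and that rule can be judged as written.

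A second reply is that the gate does little harm: it nearly always leads to Mann-Whitney, a valid test for skewed data. This also stands. A reader might infer that choosing the test from the data inflates the false-positive rate. The simulations do not support that on the unit's own figures.

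A reader might also infer that chance imbalance will readily create or conceal a 3-day difference. The figures do not support this either. The 21% event begins at a shift of about 1.4 to 2.2 days; the full 3 days is much rarer. Across all randomisations, chance imbalance is already covered by the 5% error rate. The bias is conditional on the imbalance that actually occurs.

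Last, every precision figure depends on an R² that the document does not give. The direction is secure; the size is a range.

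**Conclusion.** The point holds as a matter of efficiency and interpretation, not validity. The stated rule replaces a choice that the plan's own figures could settle with one made on the trial data, almost always ends in a test that alone does not estimate the 3-day target, and leaves a recorded predictor unused.

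The sizes rest on a lognormal fitted to the unit's median and mean, on R² of 0.2 to 0.5 (assumed), and on unstratified allocation. The adjustment is worth making, but it does not rescue the power. Even at R² = 0.5 it reaches only 42% for 12 to 9 days. The SD of 3.83 is a separate problem: a mean-median gap of 7 days implies an SD of at least 7 in the unit's own data, and no covariate repairs that.

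**What to change.** For the primary outcome, delete the normality check and pre-specify one analysis adjusted for gestational age at birth as a continuous covariate. Either of two models would serve:

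- **Linear model of log duration**, with the gain in precision shown in step 6.
- **Proportional-odds regression**, the covariate-adjusted relative of Mann-Whitney. The gain is in power; a narrower CI for the log odds ratio should not be promised.

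With either, report a covariate-adjusted (standardised) difference in median days with a bootstrap 95% CI, so that the result speaks to the 3-day target. Keep the unadjusted Mann-Whitney as a sensitivity analysis.

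Settle the choice before anyone sees outcomes by arm, and preferably before the interim analysis at half the sample, since the trial is not blinded. The cost is a protocol amendment, matching wording in any SAP, and slightly more analysis work. No new data or infants are needed.
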